## Abstract

Obsessive–Compulsive Disorder (OCD) is a chronic psychiatric condition with a lifetime prevalence of 2–3%. It significantly burdens quality of life and is associated with substantial economic and disease burdens. Cognitive-behavioral therapy and high-dose selective serotonin reuptake inhibitors are considered the first-line treatments for OCD. Approximately two-thirds of patients with Obsessive–Compulsive Disorder (OCD) exhibit inadequate responses to current standard therapies, thus lacking adequate therapy, resulting in a loss of quality of life and huge economic burdens. Repetitive transcranial stimulation (rTMS) is a non-invasive, safe, and well-tolerated intervention that modulates prefrontal cortical circuits involved in OCD. A previous systematic review explored the therapeutic effects of rTMS applied to the dorsolateral prefrontal cortex (dlPFC) area in patients with treatment-resistant OCD. It showed that the application of high-frequency and low-frequency (LF) rTMS to the dlPFC region yielded controversial post-treatment Y-BOCS (Yale-Brown Obsessive–Compulsive Scale) findings due to factors such as small sample sizes, short-term study durations, and variations in rTMS protocols. Objectives: Thus, we propose a theoretical protocol based on previous findings to assess better the effect of LF rTMS for treatment-resistant OCD patients. Methods: We will recruit patients with moderate to severe OCD and limited response to previous treatments from in- and outpatient clinics. We will use fMRI for precious localization of the right dlPFC and application of 1 Hz stimulation of in total 2000 pulses with three times 40 s inter-train intervals 5 days a week, in 6 consecutive weeks. The primary outcome will be the mean reduction in Y-BOCS at the end of this study. Conclusions: This study highlights rTMS’s potential to reform OCD treatment, accentuate safety, accessibility, clinical integration, and future research foundations.

## 1. Introduction

Obsessive–Compulsive Disorder (OCD) is a chronic psychiatric condition characterized by intrusive, repetitive, and distressing thoughts (obsessions), as well as repetitive behaviors or mental acts (compulsions)—which may be overt or covert—that often consume a significant amount of time. These compulsions are typically carried out to neutralize the fear and anxiety triggered by the obsessions, and the disorder is frequently accompanied by varying levels of insight [1].

With a lifetime prevalence of 2–3%, OCD imposes a significant burden on quality of life and is associated with substantial economic and disease burdens [2,3,4]. First-line standard therapy for OCD patients is cognitive-behavioral therapy (CBT) with or without additional selective serotonin reuptake inhibitors (SSRIs). However, 20–60% of these patients experience non-response to these first-line therapies [5]. Following this, second-line treatment would include the interchange of SSRI, Clomipramine, or serotonin noradrenalin reuptake inhibitors (SNRI), with additional add-on treatments [6]. Still less than 10% are currently receiving evidenced-based treatments, highlighting the need for alternative treatments and moving forward to interventional options [6]. The situation of untreated or neglected patients underscores the urgency to explore safe therapeutic alternatives [7].

From a mechanistic standpoint, OCD is closely linked to dysregulation within cortico-striato-thalamo-cortical (CSTC) circuits, which encompass the orbitofrontal cortex, striatum, thalamus, and related subcortical structures [8]. Within this circuitry, the dorsolateral prefrontal cortex (dlPFC) plays a pivotal role in regulating working memory and executive function. Aberrations in front-limbic networks, including those involving the dlPFC, contribute to maladaptive fear responses, intolerance of uncertainty, and the persistence of compulsive behaviors [9,10,11]. Despite ongoing refinements, prevailing neurocircuit models often fail to fully account for the complexity of OCD, including co-occurring psychiatric conditions and the dynamic, longitudinal course of symptoms. In this context, Gonaçalves et al. (2011) offered a medical hypothesis proposing that OCD may arise in part from interhemispheric imbalances in CSTC circuits, potentially linked to difficulties in sensory and cognitive filtering at the thalamic level. According to this perspective, effective interventions—particularly those involving cognitive-behavioral therapy or neuromodulatory approaches—could not only alleviate OCD symptoms but also induce measurable neuroplastic changes in these circuits. Non-invasive brain stimulation (NIBS) approaches possess the capacity to restore functional interhemispheric balance by modulating the excitability and connectivity of specific cortical regions. This comprehensive perspective highlights the necessity for a more sophisticated and dynamic comprehension of OCD pathophysiology, transcending static models and integrating the brain’s intrinsic ability for adaptive remodeling in response to treatment [11].

However, existing neurocircuit models often neglect co-occurring psychiatric conditions and longitudinal changes in symptoms, warranting a comprehensive approach to understanding and treating OCD. Repetitive transcranial magnetic stimulation (rTMS) is a non-invasive neurostimulation technique that modulates neuronal activity via magnetic pulses delivered by a wire coil through the scalp, leading to long-lasting effects on the brain [12]. Due to its impact on chronic brain disorders, several TMS devices have been FDA-approved for treatment-resistant major depressive disorder since 2008, and new indications are currently under development [13].

rTMS exerts selective influence over specific brain regions, using different stimulation protocols with various physiologic purposes [12]. Generally speaking, low-frequency (LF) rTMS inhibits, and high-frequency (HF) rTMS excites. Assessing neurostimulation response is challenging due to potential effects on surrounding areas and circuits, complicating clinical evaluation [9]. Studies targeting dlPFC in major depression disorder (MDD) reveal varied excitability in regions like the somatosensory cortex, subgenual anterior cingulate cortex, superior parietal lobe, and temporal regions [14].

Current research on rTMS in OCD lacks a definitive protocol for treatment-resistant patients. A meta-analysis by Fitzsimmons et al. displayed the medial frontal cortex and the dlPFC as promising options [15]. A more specific network analysis of the different protocols revealed significant effectiveness for LF right dlPCF stimulation, HF bilateral dlPFC stimulation, and LF stimulation of the pre-supplementary motor area (pre-SMA). Additionally, the accelerated continuous theta-burst stimulation (cTBS), a specific kind of rapidly fast rTMS, on the SMA in treatment-resistant OCD patients significantly improves psychopathology, severity of illness, and depression among those patients [16]. All studies showed the common side effects of rTMS, including headaches, scalp discomfort, muscle spasms, mood changes, and less common seizures [17]. These are mostly mild and reversible, suggesting that rTMS is safe. Moreover, the FDA approved a TMS system by Brainsway for OCD based on the lack of serious adverse events in one revised trial [2,18].

However, this approved alternative is for deep TMS and, therefore, requires a specific coil to stimulate deep brain areas, which limits its availability in a wide real-world setting [19]. Our theoretical trial will focus on rTMS, as the needed coils will be more available. While different targets are potentially effectual, the right dlPFC seems the most effective in the general OCD population [15,20]. Unfortunately, conflicting evidence exists in treatment-resistant patients [21]. Moreover, the standard assessment of the optimal localization of stimulation of the dlPFC lacks accuracy. A study by Zhang et al. found that the dlPFC, assessed by the 5 cm rule, was meticulous in 13.8% to 54% [22]. Therefore, there is a need for an MRI-based neuronavigation to localize the dlPFC exactly individually to reduce side effects in other areas and improve the efficient investigation of treatment in this area.

Consequently, this theoretical trial seeks to determine the efficacy and safety of low-frequency repetitive transcranial magnetic stimulation (LF rTMS) applied to the right dorsolateral prefrontal cortex (dlPFC) in conjunction with standard therapy for treatment-resistant Obsessive–Compulsive Disorder (OCD) in adults. The hypothesis postulates that the rTMS protocol will result in a statistically significant reduction in Yale-Brown Obsessive Compulsive Scale (Y-BOCS) scores compared to a sham intervention in patients undergoing standard therapy over 6 weeks.

## 2. Methods

### 2.1. Trial Design

This trial will be a phase II multicentric, sham-controlled, parallel trial. Eligible patients will be randomly assigned in a 1:1 ratio to receive either low-frequency rTMS of the right dlPFC or sham rTMS, both in conjunction with standard therapy.

Given the relatively low prevalence of treatment-resistant OCD, patient recruitment will be conducted across multiple outpatient psychiatric centers in the United States to ensure adequate participant enrollment.

### 2.2. Randomization

#### 2.2.1. Randomization Sequence Generation

Eligible participants who provide informed consent after the baseline visit will be randomized and assigned in a 1:1 ratio to one of the two intervention groups, stratified by site. Randomization will be conducted using a computerized, web-based system called Interactive Response Technology (IRT). This approach ensures a balanced distribution of key covariates across the study sites. The centralized IRT system will generate the allocation sequence and assign the code corresponding to either active or sham rTMS. The study coordinator will implement the allocation specified by the IRT system.

Each site’s delegated physician or clinical research investigator will discuss the trial information with participants and obtain and document informed consent. Prior to any study visit or procedure, participants willing to participate will receive comprehensive information about the study and complete the informed consent process. During the screening visit, participants will have at least 24 h to review the study information before providing consent. After verifying eligibility criteria and obtaining informed consent, investigators will enroll the participants in the study and proceed with randomization.

#### 2.2.2. Allocation Concealment

At each study site, a designed person will conduct pre-screening and assess participant eligibility following the competition of the informed consent process. This person is responsible for initiating the randomization procedure. Therapy assignments will remain concealed until the investigator performing the randomization has: 1. identified themselves (i.e., verified their identity within the randomization system), 2. confirmed the participant’s eligibility (i.e., ensured that the participant definitely meets all inclusion criteria), and 3. documented confirmation (i.e., recorded the eligibility confirmation in written form to the central randomization office through the REDCap platform (https://www.project-redcap.org, accessed on 25 November 2024). This approach ensures that the allocation concealment is maintained, thereby preventing selection bias and ensuring the integrity of the randomization process.

#### 2.2.3. Implementation

The implementation of randomization is strictly limited to trained and designated professionals who uphold the integrity of the study, irrespective of researchers’ preferences or participants’ conditions. An independent researcher will generate the allocation sequence by creating randomization cards using computer-generated random numbers. The original allocation sequences will be securely stored in an inaccessible location, and only copies of these sequences will be used during the study to prevent unauthorized access or alterations. To avoid confusion between treatment codes (e.g., A and B), the allocator will maintain a detailed and secure record that maps each code to its corresponding treatment (rTMS or sham). This ensures that the executing technicians can accurately implement the treatment assignments without ambiguity. By centralizing the randomization process and restricting access to the allocation sequence, the study maintains robust control over the assignment process, thereby enhancing the reliability and validity of the study outcomes.

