### 2.3. Blinding

#### 2.3.1. Blinding

To minimize bias and ensure the study’s integrity, participants and researchers will be blinded to the treatment assignments. Blinding will be achieved through the use of a purpose-built sham TMS coil equipped with a magnetic shield that attenuates the TMS effects. Additionally, surface electrodes will be added to stimulate the skin during a TMS pulse, producing somatosensory effects in the skin and peripheral nerves similar to those from an intervention. This combination ensures that participants cannot discern whether they are receiving active or sham treatment based on sensory feedback. All individuals involved in the study—including participants, healthcare providers, assessment researchers, and data analysts—will remain blinded to the treatment allocations throughout the study to reduce potential biases. Each participant will receive a unique code, to facilitate data analysis without revealing information about the treatment groups. This method helps to maintain objectivity in the evaluation outcomes. The executing technician tasked with setting up the treatment will be aware of the specifics but will not engage with other participants, including the healthcare provider or the study participants.

A third person who will serve as clinical sub-investigator will be responsible for participants’ enrollment and conduction of follow-up visits complying with the criteria of Good Clinical Practices and Human Subjects Research. Each center will require some clinical sub-investigators who will receive relevant protocol information and complete training. In case of minor adverse events, these can be discussed with the principal investigators without the need for unblinding. Participants will be unblinded 6 months after the end of the study. This delayed unblinding ensures that the primary data collection and analysis phases are free from bias while still providing participants with information about their treatment allocation once the study objectives have been met. By implementing these rigorous blinding procedures, the study aims to ensure an objective assessment of treatment effects, enhance the reliability of the findings, and uphold the highest standards.

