#### 2.3.2. Emergency Unblinding

Patients must be unblinded to provide the best possible care if serious neurological or psychiatric side effects or adverse events such as sudden and significant changes in mood, thinking, or neurological function occur after the rTMS procedure. These include seizures or neurological deficits, an increase in severity of depression (marked by changes in the HDRS ≥ 25), and manic symptoms like psychotic symptoms. Further changing warning signs of suicidal ideation, based on the nomenclature from the National Institute of Mental Health, like talking about the want to die or feeling unbearable pain [23], will lead us to assess the suicidal ideation attribution with the SIDAS score [24]. In case of a score ≥21, this will also lead to unblinding.

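### Section 2.2.3 uses treatment codes shared across an arm, so a mandatory unblinding of one patient could disclose other patients' arms to anyone who can see the codes

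*Protocol article*

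**What the plan says.** Four parts of the protocol article bear on this.

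- **2.2.1 Randomization Sequence Generation.** On the web-based system: "The centralized IRT system will generate the allocation sequence and assign the code corresponding to either active or sham rTMS". Then: "The study coordinator will implement the allocation specified by the IRT system".
- **2.2.3 Implementation.** "To avoid confusion between treatment codes (e.g., A and B), the allocator will maintain a detailed and secure record that maps each code to its" treatment, so that the technicians can set up the right coil. On the sequence, the originals are locked away and "only copies of these sequences will be used during the study to prevent unauthorized access or alterations". The section adds that access to the sequence is restricted. It does not name who holds the copies.
- **2.3.1 Blinding.** Everyone, "including participants, healthcare providers, assessment researchers, and data analysts—will remain blinded to the treatment allocations throughout the study". The executing technician is the stated exception and is kept apart from providers and participants. Each participant also gets a unique code, described as serving data analysis.
- **2.3.2 Emergency Unblinding.** "Patients must be unblinded to provide the best possible care if serious neurological or psychiatric side effects or adverse events" occur. The listed triggers include seizure, neurological deficit, worsening depression against an HDRS threshold of 25, manic or psychotic symptoms, and a SIDAS score of 21 or more.

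**The concern.** A shared arm code is safe only while no code is ever linked to a treatment in front of someone who sees other participants' codes. Section 2.3.2 requires individual treatments to be disclosed while the trial is running. The safeguard in 2.2.3 is a secure code-to-treatment record. It does not cover this situation, because the key can be worked out from one unblinded patient without opening the record.

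Two protections are at stake. The primary outcome is a clinician-rated Y-BOCS, so knowledge of the arm could influence later ratings. Allocation concealment would also weaken for patients not yet randomized if an enrolling person could read the next assignments. Recruitment runs over 6 months and treatment lasts 6 weeks, so early patients will be under treatment while later ones are still being enrolled.

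**Working it through.** **1. Is the code arm-level?** Section 2.2.1 has the IRT assign a code that stands for active or sham. Section 2.2.3 calls these treatment codes, gives A and B as an example, and keeps one record from code to treatment. The example leaves the choice of letters open, but any code that maps to a treatment in this way is shared within the arm. The unique code in 2.3.1 is not said to replace it.

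**2. What does one unblinding reveal?** There are two codes and two arms. Suppose an observer learns that one participant with code A received active treatment. Then A is active and B is sham, and the observer knows the arm of every participant whose code they see. With a participant-specific number, the same event reveals that one participant only.

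**3. Who could be that observer?**

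| Role | What the text says | Exposure |
|---|---|---|
| Technician (2.2.3, 2.3.1) | Knows the treatment, kept apart | Learns nothing new |
| Study coordinator (2.2.1) | Implements the allocation; sight of the code and blinding status not stated | Plausible |
| Investigator performing randomization (2.2.2) | Assignment concealed until three steps are complete; what is then shown is not stated | Plausible |
| Raters, providers, analysts (2.3.1) | To stay blinded; not said to see the code | Not documented |
| Holder of sequence copies (2.2.3) | Not named; access restricted | Unknown |

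Section 2.9.1 limits each site to its own data. A site-based observer would therefore most likely see the codes of that site's participants and not of all 110.

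**4. How likely is a trigger?** Inputs:

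- Participants per arm: 55 (2.10). This reproduces: 76 participants is 38 per arm, 38 / (1 − 0.30) = 54.3, rounded up to 55, so 110 in total.
- Sessions per participant: 5 per week × 6 weeks = 30 (2.7.1).
- Seizure risk: 8 per 100,000 sessions = 0.00008 (2.7.2).

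Active sessions: 55 × 30 = 1,650.

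P(at least one seizure) = 1 − (1 − 0.00008)^1650 = 0.124, about 12%.

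This assumes that every active participant completes all sessions, that sessions are independent, and that the quoted risk applies. If 30% of the active sessions were lost, 1,155 would remain and the result would be 1 − (1 − 0.00008)^1155 = 0.088, about 9%.

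**5. The other triggers.** Their rates are not in the document. Purely as an assumption, let p be the overall chance that a participant meets any trigger. Then P(at least one unblinding among 110) = 1 − (1 − p)^110:

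| Assumed p | P(any unblinding) |
|---|---|
| 0.5% | 42% |
| 1% | 67% |
| 2% | 89% |
| 5% | 99.6% |

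These are chances that some patient is unblinded. They are only an upper limit on the chance that codes are exposed. Exposure also requires that the observer learns the unblinded patient's arm, knows that patient's code, and sees other participants' codes. The document gives no basis for those probabilities.

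**The case against.** The strongest reply is that the leak needs conditions the document never states. No section hands the codes to raters, providers or participants. The code map serves the technicians, who know the treatment anyway. Unblinding a patient means revealing that patient's treatment, and need not show the letter. The copies of the sequence are not said to be at sites, or to be written in A/B codes, and access is restricted. Custody of lists and the mechanics of a code break are also commonly left to a fuller protocol or a randomization manual.

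Most of this stands, and it makes the point conditional. A reader might infer that the first unblinding necessarily reveals the whole trial and turns the copies into a list of future assignments. The document does not support that, because it does not place codes or copies with blinded or enrolling staff. Nor may the table of assumed rates be read as the chance that both codes are exposed. A reader might also want to convert the risk into an inflated false-positive rate for the Y-BOCS comparison. That would need an assumed shift in ratings for which the document has no figure, and ratings made before the first unblinding could not be affected.

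What does not stand is that this is only missing detail. Sections 2.2.1 and 2.2.3 positively describe an arm-level code, and hiding the map does not protect against inference from an event that 2.3.2 makes compulsory. The two sections also differ on whether the IRT or an independent researcher generates the sequence. That is a separate matter, but the fix below relies on the IRT.

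**Conclusion.** The point holds as a conditional weakness in the stated method. The plan combines shared treatment codes with mandatory individual unblinding and describes no protection for the remaining participants. If the coordinator, the randomizing investigator or anyone else meant to be blinded or involved in enrolment can see the codes, one unblinding lets them infer the arm of each other participant whose code they see. If such a person also holds a copy of the sequence in those codes, it shows upcoming assignments.

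On the one documented trigger rate, the chance that at least one seizure forces an unblinding is about 12%, given full attendance and the quoted risk. Section 2.7.2 says the stimulation parameters lie below those for seizure induction and that patients at raised risk are excluded, so the seizure figure may be lower. The remaining triggers add to it by an unknown amount. The chance of actual exposure is lower than the chance of any unblinding and cannot be computed from the document. The change is worth making because participant-specific numbers remove this route of inference at almost no cost.

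**What to change.** In 2.2.3:

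- Replace the shared codes with a unique, non-sequential treatment number for each participant, issued by the IRT that 2.2.1 already plans, and state that no code is common to an arm.
- State that the system releases the coil setup participant by participant, to the technician only.
- State that copies of the sequence are kept away from anyone who enrols, treats or rates participants.

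In 2.3.2, state that an unblinding is carried out for one participant number at a time and discloses only that participant's arm. The events that lead to unblinding are not affected by this change.

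The cost is about a paragraph of wording and a setting in a system already planned, with no extra participants. The small downside is that technicians look up each participant's setup instead of working from a two-letter key.
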